### Data collection and management

Upon enrollment, detailed patient demographic data (age, sex, body weight, ethnicity), medical history, clinical data (vital signs, ECG, laboratory tests), and comorbidities are collected. Vital sign monitoring includes heart rate, systolic and diastolic blood pressure (SBP/DBP), respiratory rate, and peripheral capillary oxygen saturation (SpO2). These parameters are recorded immediately at the initiation of the study drug administration (designated as T0), with subsequent assessments performed every 20 min during the first 2 h post-administration. From 2 to 24 h post-administration, or when weaning screening criteria are met and a weaning trial is planned, recordings are taken every 2 h. Additional recordings are obtained immediately following successful weaning and/or ICU discharge. Body temperature is recorded at T0 and again at 24 h post-administration or when weaning criteria are met. Continuous ECG monitoring is conducted throughout the study drug administration. Standard 12-lead ECG is obtained, and blood samples (for complete blood count, biochemistry, coagulation profile, and pregnancy test when applicable) are collected before randomization and within 12–48 h after discontinuation of the study drugs.

The CPOT and RASS scores are evaluated as baseline assessments prior to randomization. Routine evaluations are performed immediately after T0 and every 2 h thereafter. Prior to any dose adjustment, both scores are documented. After each adjustment, assessments are repeated every 5 min until clinical targets are met and no further dose modifications are needed. If the patient is in undisturbed sleep, the RASS score is recorded as unchanged from the previous value and annotated as “sleeping”. However, for final determination of titration cessation, patients are awakened for formal CPOT and RASS evaluation.

Daily records include cumulative sedative and analgesic doses, time to successful weaning, and ICU discharge time. All adverse events and concomitant medications are systematically recorded throughout drug administration and within 12–48 h after drug discontinuation. A trained investigator at each study center is responsible for the daily screening and enrollment of patients, ensuring strict adherence to the study protocol, and completing the electronic case report form (e-CRF). All data are handled with confidentiality and anonymized to protect patient identity. Access to data is restricted to authorized personnel only. Data accuracy is subject to periodic monitoring and verification by the principal investigator to ensure compliance with regulatory and quality standards.

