## Methods

### Study design

This is a multicenter, randomized, single-blind, parallel, positive control study initiated by Yichang Humanwell Pharmaceutical Co., Ltd., China. Apart from our ICU, 15 ICUs from tertiary hospitals in China enroll patients in the trial. This study was registered at ClinicalTrials.gov (NCT06785571). The trial protocol is reported in accordance with the Standard Protocol Items: Recommendations for Interventional Trials (SPIRIT) guidelines (Calvert et al., 2018). Table 1 presents the scheduled process of enrollment, interventions, and measurements.

**TABLE 1 T1:** Scheduled process of enrollment, interventions, and measurements.

Timepoint	Study period				
	Enrollment	Allocation	Post-allocation		Close-out
	After admission to ICU	After obtaining informed consent	Before study drug administration	Study drug administration	12–48 h after study drug administration ended
Enrollment					
Eligibility screen	X	​	​	​	​
Informed consent	X	​	​	​	​
Allocation	​	X	​	​	​
Interventions					
Nalbuphine hydrochloride	​	​	​	X	​
Hydromorphone hydrochloride	​	​	​	X	​
Assessments					
Baseline variables	X	​	​	​	​
Vital signs	X	X	X	X	X
RASS score	X	X	X	X	​
CPOT score	X	X	X	X	​
Laboratory tests	X	​	​	​	X
APACHE II score and SOFA score					
Dose of drugs (study drugs, analgesics, vasopressors, rescue sedatives)	​	​	​	X	​
AEs and SAEs	​	​	​	X	​
Outcome variables	​	​	​	​	X

RASS, Richmond Agitation–Sedation Scale; AEs, adverse events; SAEs, serious adverse events.

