### Randomization and blinding

Eligible patients are allocated at a 1:1 ratio to the experimental or control group, with competitive enrollment across centers. The randomization sequence is generated and assigned via the Interactive Web Response System (IWRS). A single-blind design is used.

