### Intervention

Analgesics and sedatives administered prior to enrollment are discontinued. In the experimental group, patients receive intravenous nalbuphine hydrochloride (Yichang Humanwell Pharmaceutical Co., Ltd., China). A loading dose of 6 mg nalbuphine Hydrochloride is administered over 30 s (±10 s), followed immediately by initiation of a continuous maintenance infusion at a baseline rate of 2.0 mg/h. Five minutes after the loading dose, if the patient’s Critical-Care Pain Observation Tool (CPOT) score is greater than 2, a 2 mg supplemental bolus is given. This supplemental bolus may be repeated once, with a minimum interval of 5 min between doses, allowing up to two supplemental boluses within the first 20 min. The total dose, including the loading dose and any supplemental boluses, is capped at 10 mg, and no additional boluses are permitted beyond the initial 20-min period. Twenty minutes after the loading dose or once the cumulative dose reaches 10 mg, the maintenance infusion rate is titrated according to CPOT and Richmond Agitation-Sedation Scale (RASS) scores. Dose adjustments are made in increments of 0.5 mg/h, within a target range of 1.0–5.0 mg/h, with a minimum of 5 min between each adjustment. In the control group, patients receive hydromorphone hydrochloride (Yichang Humanwell Pharmaceutical Co., Ltd., China) via continuous intravenous infusion, initiating at 0.5 mg/h. The infusion rate is adjusted based on CPOT and RASS scores in increments of 0.5 mg/h within a target range of 0.5–3.0 mg/h, with at least 5 min between adjustments.

If a patient’s CPOT score remains above 2 despite reaching a nalbuphine infusion rate of 3.0 mg/h or a hydromorphone hydrochloride infusion rate of 2.0 mg/h, rescue sedation with propofol is initiated. Propofol is started at an initial infusion rate of 0.5 mg/kg/h and subsequently titrated in increments of approximately 25% of the current rate (0.125 mg/kg/h), within a dosage range of 0–4 mg/kg/h.

The study drug infusion is discontinued after 24 h (±10 min) of administration or earlier if the patient met weaning criteria and a spontaneous breathing trial is planned. Patients requiring ongoing analgesia or sedation after discontinuation of study drugs are managed at the investigator’s discretion.

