### Outcomes

The primary outcome is the analgesic success rate during 24 h of study drug administration. Analgesic success is defined as the fulfillment of both criteria: 1) no administration of rescue analgesic medication, and 2) maintenance of a CPOT score ≤2 for at least 70% of the observation period during study drug infusion.

The secondary outcomes include: 1) The percentage of time within CPOT score ≤2 and RASS score between −2 and +1 during 24 h of study drug administration: This metric represents the proportion of time during which a patient maintains a CPOT score of ≤2 and a RASS score between −2 and +1, relative to the total duration of study drug administration. 2) The frequency and dosage of rescue sedation during 24 h of study drug administration: The frequency refers to the number of rescue sedative administrations, while the dosage indicates the total amount of propofol administered as rescue sedation during the infusion of the study drug. 3) The proportion of patients requiring rescue sedation during 24 h of study drug administration: This is the percentage of patients in each treatment group who received concomitant propofol for rescue sedation during study drug infusion, calculated as (Number of patients receiving propofol/Total number of patients in the group) × 100%. 4) The total cumulative dose of rescue sedative during 24 h of study drug administration: The sum of all propofol doses administered as rescue sedation during the period of study drug infusion. 5) The time to successful weaning and ICU discharge during 24 h of study drug administration: Time to successful weaning is defined as the interval from the initiation of the study drug to liberation from mechanical ventilation. Time to ICU discharge is defined as the interval from study drug initiation to actual ICU discharge. Successful weaning is achieved when the patient is extubated and subsequently maintains stable spontaneous breathing without the need for reintubation. 6) The weaning success rate and the proportion of patients discharged from the ICU: The weaning success rate reflects the percentage of patients successfully weaned from mechanical ventilation. The proportion of patients discharged from the ICU indicates the percentage of patients transferred out of the ICU within the observation period.

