### Statistical analysis

Statistical analyses will be performed using SAS software (version 9.4 or higher). Continuous variables will be presented as mean ± standard deviation for normally distributed data and median ± interquartile range for non-normally distributed data, whereas categorical variables will be summarized as frequencies and percentages. All statistical tests and confidence intervals (CI) will be two-sided, with statistical significance defined as a p-value less than 0.05. The difference in analgesic success rates between the experimental and control groups will be estimated using the Miettinen and Nurminen method to calculate the two-sided 95% CI. Non-inferiority will be established if the lower bound of this interval exceeds −8%. The proportion of time during which patients maintain a CPOT score ≤2 and a RASS score between −2 and +1 will be analyzed using the arcsine square root transformation, followed by between-group comparison via the t-test. Time from initiation of study drug to successful weaning and time to ICU discharge will be illustrated using Kaplan-Meier survival curves and compared using the log-rank test. The frequency and dosage of rescue propofol sedation, along with total propofol dose administered, will be compared between groups using either the t-test or Wilcoxon rank-sum test, depending on data distribution. The proportions of patients requiring concomitant propofol sedation, weaning success rate, and ICU discharge rate will be compared using the χ^2^ test or Fisher’s exact test. The incidence of adverse events will also be assessed using χ^2^ test or Fisher’s exact test.

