### Limitations

Despite these strengths, several limitations merit consideration. First, although nalbuphine exhibits a ceiling effect for analgesia, this occurs at doses exceeding 0.4 mg/kg, which are not reached in our protocol (maximum 10 mg loading plus 5 mg/h maintenance). Within the selected dose range, dose-dependent analgesic efficacy is preserved. Nevertheless, the ceiling effect may limit efficacy in patients with very high opioid requirements, which we have acknowledged as a study limitation. Second, one limitation of our study is the lack of precise equipotent dosing between nalbuphine and hydromorphone. The chosen dose ratio (approximately 4:1) may underestimate nalbuphine’s required dose if the true potency ratio is 5-7.5:1. To mitigate this, our protocol permits supplemental boluses and upward titration to a maximum of 5 mg/h. Moreover, we will conduct sensitivity analyses using alternative potency assumptions to assess the robustness of the non-inferiority conclusion. Future dose-optimization studies in ICU patients are warranted. Third, the protocol, as described, may face challenges related to generalizability. ICUs are highly heterogeneous (Zimmerman et al., 2006), and patient populations can vary significantly between centers in terms of primary diagnoses (e.g., medical, surgical, or trauma), severity of illness, and baseline organ function. If the inclusion and exclusion criteria are too restrictive, the results may not be applicable to all subtypes of critically ill patients. Additionally, the findings will be directly comparable only to the specific positive-control analgesic chosen, conclusions may not extend to all opioids or analgesics used in the ICU. The single-blind design carries an inherent risk of assessment bias despite mitigation strategies, and the exclusion of patients with severe organ dysfunction, hemodynamic instability, or need for deep sedation further limits generalizability to the sickest ICU subpopulations. Variability in patient pharmacodynamics—especially in those with organ dysfunction, comorbidities, or concurrent sedative use—may also influence analgesic response. Moreover, the 24-h intervention period may not capture longer-term outcomes such as delirium, opioid withdrawal, or post-ICU dependence, and variations in institutional sedation protocols and nursing expertise could influence implementation fidelity across centers. These factors should be considered when interpreting results and may inform future research aimed at optimizing dosing strategies or evaluating specific subgroups.

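### Time in the joint CPOT/RASS target is compared without adjusting for the CPOT and RASS scores taken before randomization: a valid test that may give up a modest amount of precision

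*Protocol article*

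**What the plan says.** All references are to the protocol article.

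- **Outcome.** In the Outcomes section, the first secondary outcome is the proportion of study-drug time during which a patient has both CPOT ≤2 and RASS between −2 and +1. It is listed first but is not designated key.
- **Test.** Under Statistical analysis, this proportion "will be analyzed using the arcsine square root transformation, followed by between-group comparison via the t-test". No covariate and no centre term is named.
- **Baseline data.** Under Data collection and management: "The CPOT and RASS scores are evaluated as baseline assessments prior to randomization". Table 1 also ticks both scores in the column before study drug administration.
- **Centres.** Under Study design: "Apart from our ICU, 15 ICUs from tertiary hospitals in China enroll patients in the trial", which makes 16. Under Randomization and blinding: "Eligible patients are allocated at a 1:1 ratio to the experimental or control group, with competitive enrollment across centers". The Limitations section adds that "variations in institutional sedation protocols and nursing expertise could influence implementation fidelity across centers".
- **Adjustment elsewhere.** The end of the Limitations section speaks of adjusted sensitivity analyses, in conditional wording and as exploratory. They concern the primary findings and name APACHE II, concomitant sedatives and delirium. They do not name baseline CPOT or RASS, centre, or this outcome.

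**The concern.** The outcome is built from two scales, and both are read in every patient before treatment starts. A patient who begins in pain, agitated or too deeply sedated begins outside the target, so baseline status can be expected to predict some of the outcome. An unadjusted t-test leaves that predictable part in the error term and so widens the confidence interval.

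The outcome deserves some care because the primary outcome is binary and assumed to be 99% in both arms. Time in target is the planned analysis that uses the pain and sedation scores on a continuous scale. The trial was not sized for it, so whatever precision the existing data can supply is worth having.

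**Working it through.** **The plan's own figure.** The only design figure is for the primary outcome. The Farrington–Manning formula with 99% in both arms, margin −8 points, two-sided α 0.05 and 80% power gives 72.86, so 73 per group, as stated. Allowing for 12% dropout gives 73/0.88 = 82.95, so 83 per group or 166, close to the stated 168. No power or variance is given for time in target. I take 73 per group (146) as the evaluable number.

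**Assumed inputs.** R² is the share of variance of the transformed outcome explained by baseline CPOT and RASS. The article gives no value. The 80% starting power is a reference point, not a claim about this outcome.

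**Reference difference.** With 73 per arm, the standard error of a difference in SD units is √(2/73) = 0.166. A t-test has 80% power at (1.96 + 0.84) × 0.166 ≈ 0.464 SD.

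**Gain from baseline adjustment.** The residual variance is multiplied by 1 − R². The equivalent total is 146/(1 − R²). Power is Φ[(1.96 + 0.84)/√(1 − R²) − 1.96].

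| R² (assumed) | Equivalent total | Extra patients | Power |
|---|---|---|---|
| 4% | 152 | 6 | 82% |
| 9% | 160 | 14 | 84% |
| 16% | 174 | 28 | 86% |
| 25% (speculative) | 195 | 49 | 90% |

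**Cost if baseline predicts nothing.** For k covariates in N = 146, the standard error is multiplied by about √[1 + k/(N − k − 3)]. For k = 2 this is √(1 + 2/141) = 1.007, a loss of 0.7%. Break-even R² is 1 − 1/(1 + 2/141) = 1.4%, a correlation of about 0.12.

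**Centre.** Entering 16 ICUs as fixed effects is not cheap. For k = 17 (15 centre contrasts plus two scores) the factor is √(1 + 17/126) = 1.065. A simulation with fixed centres and one baseline score, with nothing prognostic, gave a standard-error ratio of 1.06. With a correlation of 0.3 and no centre effect the ratio was 1.01, so the gain from baseline was cancelled.

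A random intercept avoids most of that cost. Simulated power with estimated variance components (normal outcomes, 146 patients, 16 centres, 400 runs each, Monte Carlo error about 2 points):

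| Baseline correlation, centre share (both assumed) | t-test | Baseline model | Baseline model + random centre |
|---|---|---|---|
| 0, 0 | 80% | 79% | 79% |
| 0.2, 5% | 80% | 82% | 84% |
| 0.3, 5% | 78% | 83% | 82% |
| 0.5, 10% | 82% | 92% | 93% |

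The steps from the second to the third column are within Monte Carlo error.

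**The case against.** **The t-test is valid.** This stands. Under 1:1 randomization it is unbiased and its error rate already allows for chance imbalance. A reader might infer that imbalance threatens the result: with 73 per arm, a baseline difference above 0.2 SD arises in 2 × [1 − Φ(0.2/0.166)] ≈ 23% of trials. But at a correlation of 0.3 such a difference moves the outcome by 0.3 × 0.2 = 0.06 SD, against a standard error of 0.166 SD. The point is about precision only.

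**The gain may be small.** This largely stands. The article says that "Analgesics and sedatives administered prior to enrollment are discontinued", so baseline scores partly reflect drugs being withdrawn. It also says that "the maintenance infusion rate is titrated according to CPOT and Richmond Agitation-Sedation Scale (RASS) scores", with reassessment every 5 minutes after each adjustment until targets are met. Over a full 24 h infusion, an initial 30 to 60 minutes outside target is only 2% to 4% of the time, though more in a short infusion. Patients needing RASS −4 or −5 are excluded, which narrows the baseline range. The 25% row is therefore speculative. The low cost of two covariates is what keeps the suggestion worthwhile.

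**A plain RASS covariate would not work well.** This stands and shapes the fix. The target is two-sided, so agitated and over-sedated patients both start outside it. A linear RASS term misses much of that relation.

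**The unseen analysis plan may adjust.** It may, and that would settle the matter. But the article names the test, so this is a stated choice and not an omitted detail.

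**Centre.** A reader might infer that ignoring centre is a clear loss, or that adding it is free. Neither is supported. The article gives no size for differences between centres, its silence on stratification may be condensation, and the simulations show no clear gain over the baseline model.

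**Conclusion.** The point holds as a minor efficiency improvement to one secondary analysis. The planned t-test is valid but makes no use of baseline scores that are already collected on the scales that define the outcome. If those scores explain 4% to 16% of the variance, adjustment is worth about 6 to 28 patients on 146, or a rise from 80% power to about 82% to 86%. If they explain nothing, the standard error rises by about 0.7%. The variance share and the 80% starting point are assumptions that the article neither gives nor contradicts. Any benefit from a centre term is uncertain. A reader might infer that the trial's main conclusion is at risk. It is not: the primary non-inferiority analysis and its sample size are untouched.

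**What to change.** In the Statistical analysis section, replace the t-test for time in the joint target by a linear model on the same arcsine-square-root outcome, with:

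- treatment;
- baseline CPOT;
- baseline RASS coded as distance from the −2 to +1 range, that is max(0, RASS − 1, −2 − RASS), or simply as in or out of target.

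Use the last reading before study drug, which Table 1 schedules, and otherwise the pre-randomization reading. If the person scoring could already know the allocation at the later reading, the pre-randomization score is the safer covariate; the article does not say who is blinded. Report the adjusted difference with its 95% CI and keep the t-test as a supporting analysis.

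A random intercept for centre may be added at little cost. Sixteen fixed centre effects should be avoided, since they can cost about 6% in standard error.

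The change is one sentence and about two degrees of freedom, with no new data or patients. It should be fixed before any unblinded comparison, so that the choice of covariates cannot look data-driven.

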## Discussion

This protocol outlines a phase III, randomized, single-blind, parallel, positive-controlled clinical trial designed to evaluate the effectiveness and safety of nalbuphine hydrochloride for analgesia in mechanically ventilated ICU patients. The study is particularly meaningful as it reflects a growing emphasis on individualized and safer analgesia strategies in critical care. If nalbuphine hydrochloride demonstrates analgesic efficacy comparable to hydromorphone hydrochloride while offering a more favorable safety profile, it can provide clinicians with an important alternative to ICU analgesia. Such results could help reduce reliance on deep sedation and limit risks associated with prolonged exposure to full μ-agonist opioids. While the design of this study incorporates several notable strengths, it also has inherent limitations.

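### Copying the previous RASS forward during sleep can count unrecognised over-sedation as in-target time in secondary outcome 1

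*Protocol article*

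**What the plan says.** The protocol article, under Data collection and management, sets the routine schedule: "Routine evaluations are performed immediately after T0 and every 2 h thereafter". Around dose changes it is denser: "After each adjustment, assessments are repeated every 5 min until clinical targets are met and no further dose modifications are needed". For sleep it adds a rule for RASS only, not for CPOT: "If the patient is in undisturbed sleep, the RASS score is recorded as unchanged from the previous value", with the record annotated as sleep. There is one exception: "for final determination of titration cessation, patients are awakened for formal CPOT and RASS evaluation".

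Under Outcomes, secondary outcome 1 is "the proportion of time during which a patient maintains a CPOT score of ≤2 and a RASS score between −2 and +1", taken relative to the total duration of study drug administration. The Statistical analysis section compares it between arms by a t-test after an arcsine square root transformation. Neither section gives the sleep annotation a role.

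The primary outcome uses CPOT and rescue medication only. Secondary outcome 1 is the only listed efficacy outcome that uses RASS.

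**The concern.** The copied score replaces a measurement at the moment when sleep and drug-induced sedation are hardest to tell apart. Titration ends when the targets are met and the patient has been awakened for formal scoring, so the last score before a stable period will usually be in target. From then on, a patient who drifts below −2, looks asleep and has a CPOT of 2 or less keeps the earlier in-target RASS. Total infusion time is the denominator, so that time is counted as success.

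If this happens more often in one arm, secondary outcome 1 understates the difference in sedation depth. The Discussion makes the point relevant: "Such results could help reduce reliance on deep sedation". That is a conditional remark about implications and not a trial objective, but secondary outcome 1 is the efficacy measure a reader would look to for it. The trial is single-blind, and the Limitations section accepts a risk of assessment bias. Deciding that a patient is asleep is a judgement exposed to that risk.

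**Working it through.** The article gives no figure for secondary outcome 1 that could be reproduced. Its only computed design figure is the sample size, which concerns the primary outcome and does not enter here.

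**Inputs from the article.** Infusion of 24 h (Intervention; it may stop earlier for weaning). Routine scores every 2 h (Data collection and management). Target of CPOT ≤2 with RASS −2 to +1, over total infusion time (Outcomes).

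**Assumptions.** Each routine score stands for 2 h. Between 2 and 8 h of an infusion are flagged as sleep. The article gives neither.

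**Weight of one copied score.** 24 / 2 = 12 routine intervals. One interval is 2 / 24 = 8.3 percentage points. Four intervals (8 h) are 8 / 24 = 33.3 points. So 8.3 to 33.3 points of a patient's result rest on unmeasured RASS. In a shorter infusion each interval weighs more.

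**Three hypothetical patients.** Each has 16 h measured in target, 8 h flagged as sleep, and CPOT ≤2 throughout.

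| State during the 8 flagged hours | True value | Score copied | Flagged time removed | Flagged time out of target |
|---|---|---|---|---|
| A: RASS −4, copied score in target | 16/24 = 66.7% | 24/24 = 100% | 16/16 = 100% | 16/24 = 66.7% |
| B: natural sleep, copied score in target | 24/24 = 100% | 24/24 = 100% | 16/16 = 100% | 16/24 = 66.7% |
| C: RASS back in range, copied score −3 | 24/24 = 100% | 16/24 = 66.7% | 16/16 = 100% | 16/24 = 66.7% |

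Patient A shows the masking. Removing the flagged time does not reveal it (16/16 is still 100%); scoring it as out of target does. Patient B shows that the out-of-target version penalises natural sleep. Patient C shows that copying can also lower the result.

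**Arm level, illustration only.** Suppose 30% of one arm and 10% of the other were like patient A. With 8 h flagged, the hidden gap in means is (0.30 − 0.10) × 33.3 = 6.7 points. With 2 h flagged it is (0.30 − 0.10) × 8.3 = 1.7 points. Nothing in the article supports these percentages.

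**What the out-of-target version bounds.** It gives a lower limit for each arm's time in target. It does not by itself bound the difference between arms. If every patient in both arms had 8 flagged hours like those of A or B, each arm would read 66.7% and the recorded gap would be 0 whatever the true mix. The flagged share by arm is therefore needed beside it.

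**The case against.** The strongest reply has four parts.

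- The rule covers undisturbed sleep only. It does not extend to drug-induced unresponsiveness, and every copied record is annotated, so it can be found and re-analysed.
- How annotated records count, and which sensitivity analyses are run, is usual content for a statistical analysis plan. A criterion for sleep belongs in the full protocol or an assessment manual. Neither is shown, so their silence here is not a fault.
- Not waking sleeping ICU patients for scoring is a reasonable trade-off.
- The consequences are limited. The primary outcome does not use RASS, patients who need deep sedation are excluded at entry, and over-sedation can be reported as an adverse event.

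Most of this stands, and it limits the point to one secondary outcome. It does not remove it. The copying rule and the total-time denominator are both stated in the article, and the bias follows from applying them together. An analysis plan can decide how flagged intervals count, but it cannot recover a RASS that was not measured. Dropping those intervals from the main analysis would depart from the published denominator.

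A reader might infer that the copied value is always in target, so that secondary outcome 1 can never show over-sedation. The article does not support that. It copies the previous value whatever it was, and a score of −3 or +2 stays out of target. Patients not classed as asleep are scored as observed, and a formal awake score is taken when titration stops.

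**Conclusion.** The concern holds in a limited form. As written, the rule can count over-sedation mistaken for sleep as in-target time. It may therefore inflate secondary outcome 1 and mask a difference between arms in sedation depth. Inflation is the more likely direction after completed titration, but it is not certain, because off-target scores are copied too.

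The firm figure is 8.3 percentage points for each copied 2 h interval of a full 24 h infusion. The range of 8.3 to 33.3 points assumes 2 to 8 h flagged as sleep. The size of any hidden arm difference cannot be derived from the article, and the 1.7 to 6.7 points above are illustrations.

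A reader might also infer that the non-inferiority conclusion is at risk. The primary outcome rests on CPOT and rescue medication, so it is not directly affected. The point is worth acting on because the annotation is already collected and the remedy is cheap.

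**What to change.** Keep the published definition of secondary outcome 1 as the main analysis. Before unblinded analysis, add the following:

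1. Report the share of infusion time annotated as sleep, by arm.
2. Repeat secondary outcome 1 with flagged intervals removed from numerator and denominator.
3. Repeat it with flagged intervals scored as out of target, as a lower bound for each arm.

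The second analysis alone is not enough: it would not reveal over-sedation confined to flagged time, and it makes the denominator depend on a label given after randomisation. Do not describe secondary outcome 1 as showing no difference in sedation depth unless the result is consistent across all versions. Where the flagged share is large in both arms, say that the comparison remains uncertain even if they agree.

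The cost is one sentence in the outcome definition or analysis plan and one extra table. The out-of-target version is conservative because it also penalises natural sleep. No waking or dosing rule changes.
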